## Abstract

**Background:**

Mild cognitive impairment (MCI) is defined as a decline in cognitive state with preservation of activities of daily living. Medications such as donepezil and rivastigmine have been commonly prescribed for MCI, but their use is controversial. Acupuncture has been widely used in Korea and has been shown to improve cognitive function. The aim of this study is to evaluate the efficacy of acupuncture for MCI and investigate the effect of acupuncture on structural and functional brain changes in patients with MCI.

**Methods:**

This study is a randomized, assessor-blinded, sham-controlled trial. Fifty participants with MCI will be randomly assigned to the acupuncture group (*n* = 25) or sham acupuncture group (n = 25). The acupuncture group will receive acupuncture treatment at nine acupuncture points (GV20, EX-HN1, bilateral LI4, and ST36) twice a week for 12 weeks. The sham acupuncture group will receive sham acupuncture treatment at the same points with non-penetrating sham needles. Both groups will be restricted from all other treatments for the improvement of cognitive function. The primary outcome measure is the Digit Span Test (DST). The secondary outcome measures are the Digit Symbol Substitution Test (DSST), Korean version of Montreal Cognitive Assessment (MoCA-K), Seoul Neuropsychological Screening Battery-II (SNSB-II), Beck Depression Inventory-II (BDI-II), State-Trait Anxiety Inventory (STAI), working memory (WM) task performance score, and structural/functional brain changes. Outcomes will be assessed at screening, baseline, 4 and 8 weeks, and after the end of treatment. We will also observe adverse events. In the statistical analysis, a full analysis set and per-protocol analysis will be performed.

**Discussion:**

This randomized clinical trial aims to examine the efficacy of acupuncture treatment for MCI. Neuropsychological tests, psychological inventories for measuring depression and anxiety, and magnetic resonance imaging will be performed to investigate the underlying neurological mechanisms and the association between cognition, emotion, and brain networks following acupuncture treatment. The results of the trial will provide evidence supporting the efficacy of acupuncture and also add to the neurobiological understanding of acupuncture treatment for MCI.

**Trial registration:**

Clinical Research Information Service, KCT0002896. Registered on 25 May 2018.

**Electronic supplementary material:**

The online version of this article (10.1186/s13063-019-3446-9) contains supplementary material, which is available to authorized users.

## Background

Mild cognitive impairment (MCI) is an intermediate stage between normal aging and dementia. In MCI, there is an objective cognitive decline but independence in daily activities is preserved [1]. The prevalence rate of MCI varies from 3% to 42% in the elderly [2]. MCI is one of the predictive factors for Alzheimer’s disease (AD), and the annualized rates of conversion from MCI to AD range from 7.5% to 16.5% [3]. Because of its high conversion rate, both clinicians and researchers are interested in MCI as a parameter for the early detection and prevention of AD.

The diagnostic criteria for MCI have been updated over the past 20 years [4–7]. The most widely used criteria, suggested by Petersen et al. [5] include (1) objective memory impairment for the patient’s age, (2) essentially preserved general cognitive function, (3) largely intact functional activities, and (4) no dementia. In patients affected by MCI, working memory (WM) impairment and episodic memory deficits are commonly observed [8–10]. Because deficits in WM could be a predictor of progression to AD, evaluating and monitoring changes to WM in MCI is very important [11]. In addition, neuropsychiatric symptoms, such as depression and anxiety, are also predictors of dementia in MCI [12].

Despite the importance of MCI management, the therapeutic options are limited. According to the 2017 American Academy of Neurology (AAN) guidelines on MCI, there is no appropriate pharmacological option, and only regular exercise and cognitive training can be recommended for patients with MCI [13]. Even though cholinesterase inhibitors such as donepezil, rivastigmine, and galantamine are routinely recommended for AD, Lewy body dementia, and Parkinson’s disease-associated dementia [14], they are not indicated for MCI because they do not have a clinically meaningful effect and actually increase the incidence of gastrointestinal adverse events [15, 16]. As alternatives, antioxidants, such as vitamin E; nootropics, such as piracetam; and vasodilators, such as nimodipine and *Ginkgo biloba*, are used for MCI. However, the evidence to support their use is still weak [17, 18].

Acupuncture treatment is widely used in Asia and can be considered an alternative treatment for MCI. Systematic reviews have suggested that acupuncture may improve cognitive function in patients with vascular cognitive impairment, no dementia (VCIND) [19, 20], and amnestic MCI [21]. Clinical trials have shown that acupuncture treatment with electrical stimulation is more effective than nimodipine in patients with MCI [20, 22–24].

Several neuroimaging studies have examined the change in activity of brain regions or functional networks related to memory after acupuncture treatment; however, in those studies, a single acupoint was stimulated [25–28]. These acupuncture procedures are limited by the fact that they do not reflect real world practice, because acupuncture treatment is usually performed at multiple acupoints. A recent study has demonstrated that pragmatic acupuncture treatment with multiple acupoints improves cognitive function and increases the connectivity of functional networks in the brain [29].

Thus, we plan for the duration of acupuncture treatment to be longer than a previous study [29], and expect to elucidate its underlying neurological mechanism, particularly focusing on WM. In this study, we will evaluate the efficacy of acupuncture treatment compared to sham acupuncture. To help understand the mechanism by which acupuncture may improve cognition, we will assess cognitive function, emotional state, and structural and functional brain changes following acupuncture treatment.

## Methods

### Objectives

The aims of this study are (1) to assess the specific effect of acupuncture treatment on MCI in comparison with sham acupuncture and (2) to investigate the neurological mechanism of acupuncture treatment for MCI associated with improvement of cognition, based on magnetic resonance imaging (MRI) results.

### Design

This study will be a randomized, assessor-blinded, and sham-controlled trial (Fig. 1). This trial will be conducted at the Kyung Hee University Hospital at Gangdong (KHUGD) and Kyung Hee University Medical Center (KHUMC) in Seoul, Korea, beginning in June 2018. This protocol is presented in accordance with the Standard Protocol Items: Recommendations for Interventional Trials (SPIRIT) 2013 statement (see Additional file 1) and the SPIRIT figure (Fig. 2). The organizational structure and responsibilities of the researchers are shown in Additional file 2.

**Fig. 1 Fig1:**
[figure not shown]
Diagram of the study flow. MCI, mild cognitive impairment; fMRI, functional magnetic resonance imaging

**Fig. 2 Fig2:**
[figure not shown]
Standard Protocol Items: Recommendations for Interventional Trials Statement (SPIRIT). Overview of study process and outcome assessment. BDI-II, Beck Depression Inventory-II; CDR, Clinical Dementia Rating; d, day; DSST, Digit Symbol Substitution Test; DST, Digit Span Test; GDS, Global Deterioration Scale; MoCA-K, Korean version of Montreal Cognitive Assessment; MRI, magnetic resonance imaging; SNSB-II, Seoul Neuropsychological Screening Battery-II; STAI, State-Trait Anxiety Inventory; wk., week; F/U, follow up

### Ethical considerations

The Institutional Review Boards of the Kyung Hee University Hospital at Gangdong and Kyung Hee University Medical Center approved the study (KHNMCOH 2017–09–007-001 and KOMCIRB-170915-HR-037, respectively). Ethics approval has been obtained from the Institutional Review Board (IRB) of both clinical trial institutes. This trial complies with the Declaration of Helsinki. Each hospital’s clinical trial manager will obtain informed consent after explaining the purpose and content of the study, rights of participants, and confidentiality. Demographic characteristics, vital signs, laboratory test results, past medical history, neuropsychological test results, questionnaire results, MRI results, and informed consent forms will be collected. The data will be kept as an electronic file with a password or a document in a locked cabinet. The data will be submitted to the Sponsor, the Korean Institute of Oriental Medicine (KIOM), within 1 month of the conclusion of the study, and the investigators will keep a copy. The documents will be stored for 3 years, after which they will be shredded. Any modifications of the protocol will be approved by the IRB and updated at the protocol registration site and with the journal. If the modifications result in changes in how the patients may benefit or be harmed, trial participants will be also notified of these changes.

The research team will communicate trial findings using de-identified study information via publication in a peer-reviewed journal, and assistance of professional writers is not anticipated. No later than 2 years after completion of this trial, we will deliver a completely de-identified data set to an appropriate data archive for sharing purposes.

### Participants

#### Assessment of eligibility

Eligibility for this clinical trial will be assessed in two steps. First, a Korean version of the Montreal Cognitive Assessment (MoCA-K), Clinical Dementia Rating (CDR), and Global Deterioration Scale (GDS) will be evaluated. In eligible participants, we will then assess cognitive function using the Seoul Neuropsychological Screening Battery-II (SNSB-II), on a separate day.

#### Inclusion criteria

Inclusion criteria for patients with MCI are as follows: (1) patients aged 50–70 years, (2) patients meeting the Peterson diagnostic criteria for MCI, (3) duration of memory loss longer than 3 months, (4) educational level longer than 6 years, (5) a MoCA-K score < 23, (6) a CDR score of 0.5 and GDS grade 2–3, (7) a Modified Hachinski Ischemic Score (HIS) score ≤ 4, and (8) patients who voluntarily sign the informed consent form.

#### Exclusion criteria

Exclusion criteria for patients with MCI include the following: (1) diagnosis of dementia using diagnostic criteria from the *Diagnostic and statistical manual of mental disorder, fifth edition* (DSM-5), (2) presence of cerebral lesions or brain damage, (3) history of cerebral hemorrhage or cerebral infarction, (4) neurological disorders such as Parkinson’s disease, epilepsy, brain tumor, etc., (5) mental disorders such as major depressive disorder, schizophrenia, bipolar disorder, etc., (6) subjects who have participated in other clinical trials within the previous 4 weeks, (7) subjects who have received acupuncture treatment for cognitive impairment within the previous 4 weeks, (8) subjects using medications related to dementia (as an exception, patients with a diagnosis of MCI who have been prescribed anti-dementia medications are allowed to be included in the study after a 15-day wash-out period), (9) women who are pregnant, breastfeeding, or childbearing and do not use adequate contraception, (10) presence of typical contraindications for MRI (e.g., obstructive phobia or metal implantation), (11) subjects who have experienced hypersensitivity reactions after acupuncture treatment or are unable to cooperate with acupuncture treatment, and (12) other subjects judged by the researchers as inappropriate to participate.

#### Discontinuation criteria

Discontinuation criteria for patients with MCI include the following: (1) subjects taking additional medication, traditional herbal medicine, or acupuncture for cognitive improvement during the acupuncture treatment of this trial (acupuncture and over-the-counter medicine for other purposes not related to cognitive improvement will be allowed up to twice a week), (2) subjects who do not attend the treatment for more than four consecutive times or for more than eight times in total, (3) improving or worsening of the disease, (4) surgery or hospitalization due to accident or other diseases, (5) serious adverse events, (6) participant request, and (7) others judged by the principal investigator as inappropriate to participate. To promote participant retention and adherence, we will send a text message the day before an appointment, as a reminder.

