### Interventions

Acupuncture will be performed by specialists in Korean medicine following the details of the Standards for Reporting Interventions in Clinical Trials for Acupuncture (STRICTA) 2010 checklist (Table 1) [30]. Patients in both the acupuncture and sham acupuncture groups will receive 24 acupuncture treatments over 12 weeks at nine acupoints (GV20, EX-HN1, bilateral LI4, and ST36). In the sham acupuncture group, the acupuncture needle (a Streitberger needle) will not penetrate the skin. Streitberger needles are widely used as placebo needles in clinical trials [31–33]. During this trial, any other treatment for the improvement of cognitive function will be restricted in both acupuncture and sham acupuncture groups.

**Table 1 Tab1:** Details of acupuncture intervention

Item	Detail	Description
Acupuncture rationale	(1a) Style of acupuncture	Korean body acupuncture
	(1b) Reasoning for treatment	We selected the optimal treatment regimen based on university textbooks about the meridian and acupuncture, and a literature review of clinical trials investigating acupuncture therapy for mild cognitive impairment and dementia
	(1c) Extent to which treatment varies	None
Details of needling	(2a) Number of needle insertions per subject per session	9
	(2b) Names of points used (unilateral/bilateral)	GV20, EX-HN1, LI4 (bilateral), ST36 (bilateral)
	(2c) Depth of insertion	5–10 mm
	(2d) Response sought	None
	(2e) Needle stimulation	Manual
	(2f) Needle retention time	15 min
	(2 g) Needle type	0.30 × 30 mm, sterilized stainless steel needle (Asia-med GmbH & Co. KG, Germany)
Treatment regimen	(3a) Number of treatment sessions	24 sessions
	(3b) Frequency and duration of treatment sessions	2 sessions/week for 12 weeks
Other components of treatment	(4a) Details of other interventions administered to the acupuncture group	None
	(4b) Setting and context of treatment	Hospital outpatient department
Practitioner background	(5) Description of participating acupuncturists	Specialist in oriental neuropsychiatry or longer than 1-year career resident under the guidance of an oriental psychiatric specialist
Control or comparator interventions	(6a) Rationale for the control or comparator in the context of the research question	As placebo control, non-penetrating sham acupuncture needles will be used
	(6b) Precise description of the control or comparator	Non-penetrating acupuncture treatment at the same acupoints using a Streitberger device

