### Outcome measurement

#### Primary outcome

The primary outcome is change in the Digit Span Test (DST) score from baseline to the end of treatment. The DST is used to measure WM, attention, and concentration, and is included in the Wechsler Intelligence Scale [35, 36]. Participants will hear sets of numbers and be asked to recall the numbers forwards or backwards. The digit sequences will be progressively longer until participants cannot recall the sets of numbers twice for a particular sequence length. The DST score is calculated by summation of the maximum number of digits successfully recalled forwards and backwards. The DST will be conducted at baseline, 4 weeks, 8 weeks, and within 2 weeks of the end of treatment.

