### Sample size calculation

To assess the efficacy of the intervention, the minimal clinically important difference (MCID) of DST was considered. However, there was no well-established prior study to derive the MCID of DST. Thus, the effect size was calculated from a similar study examining acupuncture treatment for MCI.

The sample size is estimated based on the result from a previous study [29]. The mean difference in the DST score is assumed to be 0.87 and the standard deviation (SD) of that is assumed to be 0.89 between the acupuncture group and sham acupuncture group. Sample size calculation shows that a total of 44 patients is needed for 90% statistical power and 5% significance level. With an estimated dropout ratio of 10%, the necessary sample size is 50 patients (25 patients for each acupuncture group).

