### Statistical analysis

In this study, statistical analyses will be performed by an independent statistician using full analysis set (FAS) and per-protocol (PP) analyses. The FAS refers to a set that is almost identical to the intention-to-treat (ITT) ideal of including all randomized subjects, but may exclude subjects who never received the treatment or missed baseline measurement after randomization. In addition, we will perform supplementary analysis of the PP analysis group. The PP analysis group refers to a set of subjects who completed the treatment originally allocated. Compliance in this study is deemed to be satisfied only by those who have undergone more than 70% of the total number of acupuncture treatments. In other words, out of the 24 treatments, participants who do not receive treatment more than 17 times are excluded from the PP analysis group because of violation of the protocol.

All demographic and baseline characteristics of participants will be presented based on descriptive analyses. Continuous data will be presented as the average and SD and analyzed using the independent two-sample *t* test or Wilcoxon rank sum test. Dichotomous data will be presented as frequency and percentile and analyzed using the chi-square test or Fisher’s exact test.

Post-test scores will be analyzed using analysis of covariance (ANCOVA), using each group as the fixed factor and baseline score with strata factors (such as sex and age) as the covariate. Within a group, the difference pre-treatment and post-treatment will be compared using the paired *t* test or Wilcoxon singed rank test for continuous data and the chi-square test or Fisher’s exact test for dichotomous data. For repeated measures outcomes, repeated measures analysis of variance (ANOVA) will be performed to compare differences between the times of measurement.

Statistical analyses of clinical outcomes will be performed using SAS® Version 9.4 (SAS Institute, Inc.). All tests will be two-sided and a *p* value <0.05 will be considered statistically significant. We will use multiple imputations for missing data.

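### Discontinuation criterion (3) allows treatment to be stopped because the patient improves, which is the effect this fixed 24-session trial is meant to detect

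*Protocol article*

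**What the plan says.** The Discontinuation criteria section gives seven grounds for discontinuation. The third is "improving or worsening of the disease". The article attaches no threshold, instrument or assessor to it, and no other section limits it.

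The sections that bear on it are these:

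- Objectives: the first aim is "to assess the specific effect of acupuncture treatment on MCI in comparison with sham acupuncture".
- Background: "we plan for the duration of acupuncture treatment to be longer than a previous study".
- Interventions: both groups "will receive 24 acupuncture treatments over 12 weeks at nine acupoints". Table 1 gives no variation in treatment.
- Primary outcome: "The primary outcome is change in the Digit Span Test (DST) score from baseline to the end of treatment". DST is measured at baseline, weeks 4 and 8, and within 2 weeks of the end of treatment.
- Statistical analysis: "The FAS refers to a set that is almost identical to the intention-to-treat (ITT) ideal of including all randomized subjects". The PP set holds those who completed the allocated treatment, and anyone without more than 17 of the 24 sessions is excluded from it. Its role is secondary: "In addition, we will perform supplementary analysis of the PP analysis group".
- Sample size calculation: a difference of 0.87 and SD of 0.89, then "With an estimated dropout ratio of 10%, the necessary sample size is 50 patients".

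**The concern.** The trial fixes the dose and makes the course longer than in the earlier study. Criterion (3) then permits the course to end because the patient is doing well. No safety purpose is given for that half of the criterion. Two consequences follow if it is applied.

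1. **Exposure.** A participant stopped at week 8 misses 8 of 24 sessions, and one stopped at week 4 misses 16. Such participants remain in the near-ITT FAS, so any benefit lost through the shorter course dilutes the estimate.
2. **Selection of the PP set.** Stopping early enough for improvement removes a participant from the PP set. If acupuncture works, more improvers are removed from the acupuncture arm than from the sham arm, and the PP difference shrinks for a reason unrelated to adherence.

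**Working it through.** **The plan's own figure.** Inputs from Sample size calculation and Statistical analysis: difference 0.87, SD 0.89, two-sided 5%, power 90%. n per arm = 2 × (1.960 + 1.282)² × (0.89/0.87)² = 21.99, so 22 per arm and 44 in total. With 10% dropout, 22/0.9 = 24.4, so 25 per arm and 50 in total. Both stated figures reproduce; the sample size is not in question. Power from the noncentral t with 25 per arm at 0.87 is 92.3%.

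**Sessions.** Two per week for 8 weeks is 16, or 16/24 = 67%. The PP rule asks for more than 70% (0.70 × 24 = 16.8), restated as more than 17 sessions. Sixteen fails on either wording, so everyone stopped by week 8 leaves the PP set.

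**Is improvement assessed during the course?** The criterion speaks of the disease, which is mild cognitive impairment (MCI). MoCA-K is scheduled at screening and within 2 weeks of the end of treatment. SNSB-II, which contains CDR and GDS, is scheduled at screening and within 3 weeks of the end. Of the scheduled cognitive tests, weeks 4 and 8 bring DST and DSST only. A mid-course stop would therefore rest on clinical judgement or on those two tests. The article gives no expected frequency, so what follows is an illustration over a range.

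**FAS dilution.** Assumptions: benefit builds up linearly over 12 weeks, is held after a week-8 stop, and the end-of-treatment DST is obtained. Each stopped acupuncture participant loses one third of 0.87, which is 0.29. With a fraction p of that arm stopped, the difference is 0.87 − p × 0.29.

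| p stopped | FAS difference | Power, 25 per arm |
|---|---|---|
| 0 | 0.870 | 92% |
| 1% | 0.867 | 92% |
| 5% | 0.856 | 91% |
| 10% | 0.841 | 91% |
| 15% | 0.83 | 90% |

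The table ends at 15% for a reason. Under linear benefit the mean change at week 8 is 0.58. With a cut of 1.5 points, the lower of the two used below, the share above it is 1 − Φ((1.5 − 0.58)/0.89) = 15%.

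**PP selection.** Assumptions: changes are normal with SD 0.89; the sham mean is 0; the acupuncture mean is 0.87 at week 12 and either 0.58 or 0.87 at week 8. The quantity that triggers stopping correlates r = 0.5 or 0.7 with the week-12 change. Participants above a cut c of 1.5 or 2 are stopped with probability q of 0.1, 0.5 or 1, alike in both arms. With b = (c − week-8 mean)/0.89, an arm's PP mean is its week-12 mean minus q × r × 0.89 × φ(b) / (1 − q × (1 − Φ(b))).

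- *Rarely used* (q = 0.1; 0.6% to 2.4% of the acupuncture arm stopped): 0.856 to 0.866. At the low end (c = 1.5, r = 0.7, full effect by week 8): 0.87 − 0.0198 + 0.0060 = 0.856.
- *About 10% or fewer stopped*: lowest value with c = 2, q = 1, r = 0.7 and the full effect by week 8. Acupuncture loses 0.623 × 0.178/0.898 = 0.124, sham loses 0.623 × 0.032/0.988 = 0.020, and the difference is 0.87 − 0.124 + 0.020 = 0.77. About 10% of acupuncture and 1% of sham are stopped.
- *Extreme* (c = 1.5, q = 1, r = 0.7, full effect by week 8): 0.87 − 0.623 × 0.311/0.760 + 0.623 × 0.096/0.954 = 0.87 − 0.254 + 0.063 = 0.68. About 24% of acupuncture and 5% of sham are stopped.

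**The case against.** The strongest reply is that the criterion may hardly ever operate. It concerns the disease and not the DST score, and none of MoCA-K, CDR or GDS is scheduled between screening and the end of treatment. A cut of 1.5 or 2 DST points is an assumption of the illustration, not of the plan. Even with 10% stopped, which would use up the whole planned dropout, the FAS difference moves only from 0.87 to 0.841. The PP analysis is labelled supplementary, and any PP set is selected after randomisation. All of this stands, and it is why the point is minor. It does not make the wording sound: a rule that is harmless only while nobody applies it has no place in the criteria.

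It could also be said that *improving* means remission, so that treatment is no longer needed. The text does not say so, and remission would still be the intended effect ending a fixed course.

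A reader might go further in three ways that the article does not support.

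- *The primary analysis is biased through missing data.* That would need the end-of-treatment DST to go uncollected after a stop, and the decision to rest on something not recorded. The article states neither, and such detail may lie in the full protocol.
- *Unblinded practitioners could apply the rule differently by arm and disturb the type I error.* The article does not say who applies it.
- *The dilution could be taken at 24% stopped.* In this illustration that share arises only if the full effect is reached by week 8, and a stop then loses nothing. It cannot be combined with the linear loss of 0.29.

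**Conclusion.** The point holds as a minor one. Criterion (3) permits, and does not merely fail to exclude, ending treatment because of the effect under study. It would be too strong to say that the trial's exposure *is* cut short: the documents show only that it can be, at an unknown frequency.

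For the primary FAS comparison the consequence is small, at most about 0.04 DST points and 2 to 3 percentage points of power over 1% to 15% stopped. This assumes linear benefit, a week-8 stop and equal application in both arms. The supplementary PP comparison is more exposed: little changed if the rule is rare, down to 0.77 with about 10% stopped, and 0.68 only when every assumption is set against it. With equal application and a working treatment, both shifts are towards no difference.

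**What to change.** Delete *improving* from criterion (3) and keep worsening as a safety reason. One defined form would be conversion to dementia by the DSM-5 criteria already used in the Exclusion criteria. Add one sentence: participants who stop for any reason are still assessed for DST at the planned end-of-treatment window unless consent is withdrawn, and are analysed in their randomised arm. If the full protocol already says this, only the deletion is needed.

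The cost is a short amendment with IRB approval and the registry and journal updates that Ethical considerations require for any modification, plus a few assessments at visits that already exist. The sample size does not change. Recruitment was to run until November 2019, so the change could still reach participants not yet treated.
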